### Follow-up

Patients will be randomly allocated to either the treatment group or the control group and will receive the respective interventions until complete wound healing occurs or for a maximum duration of 12 weeks. Digital photography will be employed to systematically document images on a weekly basis. The researchers will determine whether the outcomes were reached. Because of the objective feature, the outcome assessment for wound healing will not be blinded or centralized. The Image J software will be utilized to quantitatively measure the area of the foot ulcer during each debridement and dressing change procedure. The total follow-up period will span one year, with evaluations conducted at 4-, 8-, 12-, 24-, and 52-weeks post-randomization to assess wound healing, ulcer recurrence, and the incidence of amputation. The items to be measured and the time window of data collection are shown in Fig 1.

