### Research design

The present study is designed as a randomized, double-blinded, placebo-controlled clinical trial and has received approval from the Ethics Committee on Clinical Trial at West China Hospital of Sichuan University (Approval No. 2023(2291)). The study will adhere to the principles outlined in the Declaration of Helsinki and the Guidelines for Good Clinical Practice. Written informed consent will be obtained from all participants prior to participation. This trial has been registered with the Chinese Clinical Trial Registry (Registration Number: ChiCTR-2400083602). In addition to receiving standard wound care, participants will be randomly allocated to either the TOT group or the sham therapy group. A schematic diagram outlining the design of this clinical trial is presented in Supporting information S1 File.

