### Randomization and allocation concealment

The eligible participants will be randomly assigned in a 1:1 ratio to either receive TOT or sham oxygen therapy. Additionally, all subjects will receive standard wound care as prescribed by their attending physician. The random sequence will be generated by a researcher utilizing R software with the simple randomization method. A designated technician will oversee the sequence numbers and monitor the treatment procedures. Both the attending physician and participants will remain blinded to the specific oxygen therapy protocol.

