### Data collection and management

The principal investigator (PI) is responsible for the design, implementation and management of the study. Other researchers are tasked with clinical diagnosis, participant screening, obtaining informed consent, administering interventions, collecting clinical samples, conducting follow-up, and ensuring data entry. A researcher will use a case report form (CRF) to collect data. A clinical trial associate will verify whether the data filled in the CRF are complete and accurate. All the personal information of subjects collected during this clinical trial will be remained strictly confidential. The data collected in the study will be stored in the hospital. The primary investigator has the access to the final dataset. The dataset without identifiable information will be available from the corresponding author on reasonable request.

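### The primary outcome, a visual judgement of wound closure, is deliberately left unmasked in a trial called double-blinded, which leaves an avoidable risk of detection bias

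*Protocol article*

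**What the plan says.** All of the relevant text is in the protocol article.

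- **Design label** (Research design): "The present study is designed as a randomized, double-blinded, placebo-controlled clinical trial".
- **Who is blinded** (Randomization and allocation concealment): "Both the attending physician and participants will remain blinded to the specific oxygen therapy protocol". No other party is named as blinded. On the sequence, the same section says: "A designated technician will oversee the sequence numbers and monitor the treatment procedures".
- **Sham** (Interventions): the control device looks and works like the active one and differs only in using ambient air as its gas source.
- **Primary outcome** (Primary outcomes): the proportion of participants whose wound is fully epithelialized within 12 weeks.
- **Who judges it** (Follow-up): "The researchers will determine whether the outcomes were reached", followed by "Because of the objective feature, the outcome assessment for wound healing will not be blinded or centralized".
- **Material available** (Follow-up): "Digital photography will be employed to systematically document images on a weekly basis". Wound area is measured with Image J. No masking of that measurement is described.
- **Staff roles** (Data collection and management): researchers other than the principal investigator have, as a group, duties that include "administering interventions, collecting clinical samples, conducting follow-up, and ensuring data entry".

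**The concern.** The article gives up masked assessment on the ground that the outcome is objective. Whether a wound has fully epithelialized is decided by looking at it, and wounds close to closure leave room for discretion. An assessor who knows or suspects the arm can resolve those cases in one direction. The same call fixes the date used for time to healing, and tracing a wound edge in Image J also involves an operator's judgement, so area reduction is exposed as well.

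At stake is the validity of the primary comparison. An error of this kind lies in the recorded outcome, so neither a larger sample, nor randomization, nor the covariate adjustment in the Statistical analysis section removes it. A reader who sees the trial called double-blinded may also assume a protection that the primary outcome does not have.

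This is a rule that the article states and justifies. It is not a detail lost when the full protocol was condensed.

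**Working it through.** **1. Reproducing the planned size** (Sample size calculation: 60% v 78%, two-sided α 0.05, power 0.80, about 100 per arm, 250 in total with about 20% dropout).

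Unpooled formula: n = (1.960 + 0.842)² × (0.60×0.40 + 0.78×0.22) / 0.18² = 7.849 × 0.4116 / 0.0324 = 99.7, so 100 per arm. The pooled formula gives 103. Dropout: 100 / (1 − 0.20) = 125 per arm, 250 in total. The plan's figures reproduce, and masking the assessment would not change them. Both sizes are used below: 100 per arm is the planned evaluable number and 125 the number randomized.

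**2. Setting the passages side by side.**

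| Element | Masked? | Section |
|---|---|---|
| Participant | yes | Randomization and allocation concealment |
| Attending physician | yes | Randomization and allocation concealment |
| Device appearance and operation | identical in both arms | Interventions |
| Judgement of wound healing | expressly not | Follow-up |
| Area measurement | not stated | Follow-up |

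The one step that the article expressly leaves unmasked is the one that produces the primary outcome.

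**3. Illustrating the size.** The misjudgement rate f is an assumption, since the article gives none. Suppose there is no true effect and 60% heal in both arms. If a share f of truly unhealed TOT wounds is called healed, the observed TOT rate is p_T = 0.60 + 0.40 f, while control stays at p_C = 0.60. With d = p_T − p_C and p̄ the mean of the two rates:

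- SE₀ = √(2 p̄(1 − p̄)/n)
- SE₁ = √([p_T(1 − p_T) + p_C(1 − p_C)]/n)
- P(reject) = 1 − Φ((1.96 SE₀ − d)/SE₁) + Φ((−1.96 SE₀ − d)/SE₁)

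Example, f = 10% and n = 125: p_T = 0.64, d = 0.04, p̄ = 0.62, SE₀ = √(2×0.62×0.38/125) = 0.0614, SE₁ = √((0.2304 + 0.24)/125) = 0.0613. The upper tail is about 9.5% and the lower about 0.4%, about 10.0% in total.

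Summing exact binomial probabilities over the rejection region of the Pearson chi-square test (the planned primary test) gives:

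| f (assumed) | Observed TOT v control | Wrong calls expected, n = 100 / 125 | False-positive rate, n = 100 | False-positive rate, n = 125 |
|---|---|---|---|---|
| 0% | 60 v 60% | 0 / 0 | 5.1% | 4.8% |
| 5% | 62 v 60% | 2 / 2.5 | 6.0% | 6.1% |
| 10% | 64 v 60% | 4 / 5 | 9.0% | 9.9% |
| 20% | 68 v 60% | 8 / 10 | 21.7% | 26.4% |

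Wrong calls are f × 0.40 × n. The normal approximation agrees closely: 6.0%, 9.0% and 21.7% at 100 per arm, and 6.2%, 10.0% and 26.0% at 125.

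**The case against.** **Assessors may be unaware of the arm.** No section says that they know it. The sham is built to be indistinguishable, and the sequence is in the hands of a designated technician. A reader might infer from the list of researcher duties that the person who runs the device also calls healing. That list is collective, so the overlap is possible but not stated. This objection stands and limits the point to a risk. It does not rescue the sentence: the article declines to require masking, so it guarantees none. If assessors are in fact masked, the sentence is wrong as written.

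**The sham still does useful work.** A reader might infer that its benefit is lost for the primary outcome. That goes too far. Participants and attending physicians stay blinded, and the Discussion says that standard care is set by those physicians without a standardized protocol. The sham therefore still guards against unequal co-treatment and changes in participant behaviour.

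**The label is not contradicted outright.** The article names two blinded parties and openly says that assessment is not blinded. The label is imprecise, but nothing is concealed.

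**The illustration may overstate the bias.** It applies f to all unhealed TOT wounds and always in favour of TOT, yet many unhealed wounds will be far from closure and not open to dispute. This stands too. Nothing in the article supports 20%, and at 5% the inflation is about one percentage point.

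**No confirmation rule is stated.** A reader might infer that closure is called at a single time point. The text does not say so: healing is counted within 12 weeks, with weekly photographs and scheduled evaluations. Confirmation of closure is a separate matter, which the full protocol may cover.

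**Conclusion.** The point holds as a risk of detection bias in the primary outcome, time to healing and area reduction. The stated reason for leaving assessment unmasked does not fit an outcome judged by eye, and the trial already has what it needs to avoid the problem.

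The size is not known. Under the assumptions above (no true effect, 60% healed in both arms, errors only in favour of TOT), misjudging 5% to 20% of unhealed TOT wounds would raise the two-sided false-positive rate from about 5% to between about 6% and 22% at 100 per arm, or 6% and 26% at 125 per arm. The lower end is small. At 125 per arm, five wrong calls among about 50 unhealed wounds roughly double the error rate.

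The documents do not support a claim that assessors know the arm, that bias has occurred, or that the sham is without value. The unmasked rule names wound healing only, so it is not extended here to recurrence.

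**What to change.** Replace the sentence in Follow-up. State that 12-week healing and wound area are determined in one of two ways:

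- by the attending physician, who is already blinded; or
- from the existing weekly photographs, coded to hide the arm and read by an existing team member who neither delivers the device nor holds the sequence.

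If unmasked assessment is kept, change Research design to say that only participants and attending physicians are blinded and that the outcome assessor is not.

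The cost is small. The first route uses someone already masked, and the second adds the work of coding image files. Neither changes the sample size, the definition of the endpoint, or the text on when treatment ends.

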**Fig 1 pone.0324475.g001:**
[figure not shown]
The schedule of enrolment, interventions, and assessments.

### Adverse events

The incidence of all adverse events, whether reported by participants or observed by the research investigator, will be meticulously documented in accordance with the study protocol. Appropriate interventions will be promptly implemented in response to the severity of each adverse event. In the case of serious adverse events, it is imperative to notify both the expert committee and the ethics committee within 24 hours.

### Data collection and management

The principal investigator (PI) is responsible for the design, implementation and management of the study. Other researchers are tasked with clinical diagnosis, participant screening, obtaining informed consent, administering interventions, collecting clinical samples, conducting follow-up, and ensuring data entry. A researcher will use a case report form (CRF) to collect data. A clinical trial associate will verify whether the data filled in the CRF are complete and accurate. All the personal information of subjects collected during this clinical trial will be remained strictly confidential. The data collected in the study will be stored in the hospital. The primary investigator has the access to the final dataset. The dataset without identifiable information will be available from the corresponding author on reasonable request.

### Statistical analysis

R software will be utilized to conduct statistical analyses. The multiple imputation approach will be utilized to address missing data. Statistical analysis will be conducted using an intention-to-treat approach. Specifically, the chi-square test will be utilized to evaluate the primary outcome measure, namely the wound healing rate at 12 weeks. For sparse data, Fisher’s exact test will be used. Logistic regression analysis will be conducted to investigate potential confounding factors that may influence wound healing. Confounding factors, such as sex, age, history of diabetes, ulcer categories, wound area, and infection status, will be adjusted to ensure the reliability of the findings. Subgroup analysis will be conducted according to age, wound categories, and wound area. The reduction rate of ulcer area and wound healing time at 12 weeks were evaluated using either the independent t-test or the Mann-Whitney, contingent upon meeting the assumptions for parametric analysis. Furthermore, the chi-square test will be applied to assess the ulcer recurrence rate and the amputation rate. Kaplan-Meire survival analysis will be performed to compare wound healing between the two groups, with the log-rank test used for statistical comparison. Unadjusted and adjusted Cox proportional hazards models were employed to evaluate the association between TOT therapy and wound healing. Multivariable models were adjusted for covariates such as age, sex, history of diabetes, ulcer categories, wound area, and infection status. A significance level of P < 0.05 will be considered statistically significant.

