#### Inclusion criteria.

① Participants must be aged between 18 and 80 years; ② Participants are required to reside in regions with an elevation of no less than 2,500 meters above sea level; ③ Chronic refractory wounds are defined as those that have not healed within a four-week period, including chronic diabetic skin ulcers and venous insufficiency ulcers of the lower limbs; ④ Adequate blood flow is required, as evidenced by an Ankle-Brachial Index (ABI) of 0.6 or higher, or a transcutaneous oxygen tension exceeding 30 mmHg; ⑤ The ulcer area must measure between 1 and 20 cm^2^.

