### Sample size calculation

The study conducted by Blackman demonstrated that the 12-week ulcer healing rate in the standard treatment group for diabetic foot ulcers was 42.8%, whereas the wound healing rate in the group receiving TOT was significantly higher at 85.2% [17]. Our previous research documented a wound healing rate of 69% in the standard treatment group for diabetic foot ulcers [22]. Assuming a baseline wound healing rate of 60% in the standard treatment group over a 12-week period, it is hypothesized that the incorporation of TOT would result in a 30% relative improvement in the wound healing rate, i.e., from 60% to 78%. This hypothesis will be evaluated using a two-sided test with a significance level (α) of 0.05 and a statistical power (1-β) of 0.8. Sample size estimation, conducted using PASS 15 software and based on the methodology for comparing two-group proportions in a randomized controlled trial, indicated that each experimental and control group should comprise approximately 100 participants, totaling 250 participants when accounting for an expected dropout rate of approximately 20%.

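### The unadjusted chi-square is a valid primary test, but making the already planned baseline-adjusted model primary could gain precision at little cost

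*Protocol article*

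**What the plan says.** The Statistical analysis section names one test for 12-week complete healing: "the chi-square test will be utilized to evaluate the primary outcome measure, namely the wound healing rate at 12 weeks". A fallback follows: "For sparse data, Fisher’s exact test will be used". The framework is set by "Statistical analysis will be conducted using an intention-to-treat approach" and "The multiple imputation approach will be utilized to address missing data".

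The covariates appear in a separate model: "Logistic regression analysis will be conducted to investigate potential confounding factors that may influence wound healing". The list is "Confounding factors, such as sex, age, history of diabetes, ulcer categories, wound area, and infection status, will be adjusted". Age, wound category and wound area are also the planned subgroup factors.

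Two other sections bear on the point. Under Inclusion criteria, "The ulcer area must measure between 1 and 20 cm" squared, and both diabetic and venous ulcers are eligible. Under Randomization and allocation concealment, the sequence is generated by simple randomisation at 1:1, with no stratification described.

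The Sample size calculation compares two proportions, 60% v 78%, at two-sided 0.05 and 80% power. It arrives at about 100 per arm, or 250 in total after about 20% dropout.

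**The concern.** Eligible wounds differ 20-fold in area (1 to 20 cm²) and have more than one cause. The plan itself treats area, category, diabetes, infection, age and sex as factors that may bear on healing. The primary test uses none of them.

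The plan justifies the adjusted model as a check on confounding. In a randomised trial the main reasons to adjust for baseline variables are precision and chance imbalance, and both are reasons to put the covariates in the primary analysis. Simple randomisation makes the second more relevant, because the design does not balance the arms on any of these factors.

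What is at stake is precision. Planned power is about 80%, and the Discussion concedes that recruiting enough participants at high altitude may be difficult. Precision that needs no extra patients is therefore worth having.

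**Working it through.** **Inputs from the protocol article.** Healing 60% (control) and 78% (TOT); two-sided α 0.05; power 0.80; 1:1 simple randomisation; six named covariates; dropout 20%.

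**Input not in the document.** The prognostic strength of the covariates. It is assumed below, from none (AUC 0.50) to strong (AUC 0.83).

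**1. Reproduce the stated sample size.**

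- Unpooled variance: n = (1.960 + 0.842)² × (0.60×0.40 + 0.78×0.22) / 0.18² = 7.849 × 0.4116 / 0.0324 = 99.7 per arm.
- Pooled variance under the null (mean rate 0.69): n = [1.960√(2×0.69×0.31) + 0.842√0.4116]² / 0.18² = (1.282 + 0.540)² / 0.0324, or 103 per arm after rounding up.
- Dropout: 100 / 0.8 = 125 per arm, 250 in total.

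The stated figures reproduce. Power of the unadjusted test is 79.0% at 100 per arm, and 87.3% if all 125 per arm were fully observed.

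**2. Power with and without adjustment.** The simulation used simple randomisation of 200 participants (100 per arm on average) and six independent covariates of equal weight. It compared the Pearson chi-square with the Wald test of treatment in a logistic model containing all six. There were 4,000 trials per row for power and 3,000 for type I error (60% in both arms). R² is the variance of the control-arm healing probability divided by 0.60 × 0.40.

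| Assumed AUC | R² | Power, chi-square | Power, adjusted | Change (points) | Type I error, chi-square / adjusted |
|---|---|---|---|---|---|
| 0.50 | 0 | 78.6% | 78.4% | −0.2 | 4.6% / 4.8% |
| 0.64 | 0.05 | 78.8% | 80.1% | +1.3 | 5.4% / 5.5% |
| 0.70 | 0.12 | 80.0% | 83.6% | +3.6 | 4.9% / 5.0% |
| 0.77 | 0.22 | 79.6% | 87.1% | +7.5 | 5.2% / 5.5% |
| 0.83 | 0.31 | 78.8% | 89.8% | +11.0 | 5.1% / 5.4% |

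Each power figure has a simulation standard error of about √(0.79×0.21/4000) = 0.6 points.

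**3. Cross-checks.**

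- A separate simulation with two covariates (1,500 trials per scenario, likelihood-ratio test) gave 79.7% to 82.0% at AUC 0.65, 78.9% to 84.7% at 0.72, and 81.2% to 89.3% at 0.78.
- The approximation n × (1 − R²) gives 103×0.95 = 98, 103×0.90 = 93, 103×0.80 = 83 and 103×0.70 = 73 per arm (rounded up) for 80% power at R² of 0.05, 0.10, 0.20 and 0.30.

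**4. Chance imbalance.** As an illustration, take a factor present in 51.9% of participants, the diabetic-foot share that the Background reports for elderly plateau patients. With 125 per arm, the standard deviation of the between-arm difference is √(2×0.519×0.481/125) = 6.3 points. A gap above 10 points has z = 10/6.3 ≈ 1.58, a probability of about 11%.

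**5. Room for the model.** At 100 per arm, 40 + 22 = 62 participants are expected to be unhealed. Treatment plus six one-parameter covariates is 7 parameters, so 62/7 ≈ 9 unhealed per parameter. An ulcer category with more than two levels lowers this.

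**The case against.** The strongest reply is that nothing here is wrong. The chi-square is valid under simple randomisation, its simulated type I error is 4.6% to 5.4%, and the sample size was computed for exactly this comparison. The adjusted model is already planned, so a chance imbalance would be examined anyway. All of that stands, and it limits the point to forgone efficiency.

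A reader might infer more than the document supports:

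- **That strong predictors are ignored and power is wasted.** The article says only that the factors may influence healing and gives no figure. The loss could be nil, and the trial is not underpowered by its own calculation.
- **That there are two competing primary answers.** One test is assigned to the primary outcome. The logistic model is described separately and is not called primary.
- **That the chi-square cannot be used with multiple imputation.** The article gives no pooling rule, a detail it may leave to the analysis plan, and workable rules exist. In a simulation with 125 per arm and 20% missing at random positions, type I error was 5.4% for a Rubin-pooled risk difference and 5.1% for the D2 rule for chi-square statistics. Simply averaging the chi-square statistics gave 9.7%, but the article does not propose that.
- **That an odds ratio will be misread.** At the planned rates the odds ratio is (0.78/0.22)/(0.60/0.40) = 2.36 against a risk ratio of 0.78/0.60 = 1.30. Nothing says that the primary effect will be given as an odds ratio. The contrast matters only for how the logistic model is reported if it becomes primary.

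It is also fair that six covariates with about 62 unhealed participants call for restraint, and that diabetes and ulcer category may largely overlap.

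**Conclusion.** The point holds as a recommended improvement, not as an error. The primary analysis forgoes whatever precision the named covariates carry, and simple randomisation leaves their balance to chance. The size depends entirely on an assumption: about 0, 1, 4, 8 or 11 points of power at 100 per arm for AUCs of 0.50, 0.64, 0.70, 0.77 or 0.83. Type I error stayed near 5% throughout.

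These figures assume independent covariates and a correctly specified model, so a poorly chosen covariate form would gain less. They come from the Wald test of the treatment coefficient. A test on the standardised risk difference was not simulated, although the 1 − R² approximation on the proportion scale gives gains of similar size (83.1% at R² 0.10 and 87.3% at R² 0.20, against 79.0%). With no prognostic value the difference was 0.2 points, so little is at risk in making the change.

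**What to change.** Make the already planned logistic model the primary analysis.

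- **Covariates:** a closed, prespecified list measured at baseline only: log wound area, ulcer category, diabetes, baseline infection, age and sex. Merge ulcer category and diabetes if they largely overlap, in view of the roughly 62 unhealed participants expected.
- **Reporting:** standardise the model to a risk difference and a risk ratio with 95% CI, so that the result is on the scale of the 60% v 78% hypothesis.
- **Missing data:** pool these estimates over imputations by Rubin's rules.
- **Sensitivity analysis:** keep the unadjusted comparison.

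The sample size need not change, because the unadjusted calculation remains a reasonable basis. The cost is a wording change and the discipline of fixing the covariate list and its form before unblinding. No new variables should be needed, since the plan already names all six. The article does not list the case report form's contents, however, so confirm that infection status is recorded at baseline. If the covariates prove weakly prognostic, the gain will be close to zero.

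### Wound healing time is assigned to a t-test or Mann-Whitney with no rule for the 40% of controls and 22% of TOT participants expected to be unhealed at week 12, alongside survival analyses of the same outcome and no statement of which governs

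*Protocol article*

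**What the plan says.** All places are in the protocol article.

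- **Secondary outcome:** time to ulcer healing is the time to complete closure of the wound. No value is defined for a wound that stays open.
- **Statistical analysis, assigned test:** "The reduction rate of ulcer area and wound healing time at 12 weeks were evaluated using either the independent t-test or the Mann-Whitney", with the choice depending on whether parametric assumptions are met.
- **Statistical analysis, further on:** a Kaplan-Meier "survival analysis will be performed to compare wound healing between the two groups, with the log-rank test used for statistical comparison", followed by unadjusted and adjusted Cox models for wound healing.
- **Statistical analysis, general rules:** an intention-to-treat approach, and multiple imputation for missing data.
- **Sample size calculation:** a "30% relative improvement in the wound healing rate, i.e., from 60% to 78" per cent; "each experimental and control group should comprise approximately 100 participants", "totaling 250 participants when accounting for an expected dropout rate of approximately 20" per cent.
- **Withdrawal of individual subjects:** withdrawal is advised for, among other reasons, less than a 20% reduction in ulcer size after four weeks of therapy.
- **Follow-up:** treatment lasts until healing or at most 12 weeks, with assessments at weeks 4, 8, 12, 24 and 52.

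**The concern.** A wound still open at week 12 has a healing time known only to exceed 84 days. A t-test or Mann-Whitney needs one value per participant, so someone must decide what to do with the unhealed, and the text does not decide it. This is not a detail left to a later document: the article names a test for this endpoint, and that test takes no account of censoring.

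Two handlings are possible, and they behave very differently.

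- **Healers only.** The compared groups are then defined by the outcome and differ in composition between arms. Randomisation no longer protects the comparison, and a real acceleration of healing can be largely hidden.
- **Everyone, with the last observed time entered as the value.** This is close to harmless if all unhealed participants are seen to day 84. It is not harmless if follow-up ends earlier in some of them, because a short follow-up then counts as fast healing.

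The section also plans survival methods for wound healing without ranking the two approaches. One secondary endpoint can therefore return two p-values that disagree, with nothing in the plan to settle which is reported as the result.

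**Working it through.** **1. The plan's own sample size.** Inputs from Sample size calculation: 60% v 78%, two-sided α 0.05, power 0.80. With unpooled variance, n per arm = (1.960 + 0.842)² × (0.60×0.40 + 0.78×0.22) / 0.18² = 99.7, so 100. The pooled formula gives 103. Allowing for 20% dropout, 200 / (1 − 0.20) = 250. The stated figures reproduce, so about 100 evaluable per arm is the right basis for power.

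**2. Participants without a healing time at week 12.** Control 1 − 0.60 = 40%; TOT 1 − 0.78 = 22%. With 100 evaluable per arm: 40 + 22 = 62 of 200, or 31%.

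**3. Size of the contrast.** The documents give no distribution of healing times. Assumption: constant hazards that reach 60% and 78% at day 84.

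- Control hazard: −ln(0.40)/84 = 0.01091 per day. TOT hazard: −ln(0.22)/84 = 0.01803 per day. Ratio 1.65.
- Restricted mean time to healing over 84 days = (proportion healed)/(hazard). Control 0.60/0.01091 = 55.0 days; TOT 0.78/0.01803 = 43.3 days. Difference 11.7 days.
- Mean among healers = (restricted mean − 84 × proportion unhealed)/(proportion healed). Control (55.0 − 33.6)/0.60 = 35.7 days; TOT (43.3 − 18.5)/0.78 = 31.8 days. Difference 3.9 days.

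The healers-only comparison shows about a third of the benefit (3.9/11.7).

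**4. Power at 100 evaluable per arm, same assumption, no further loss (simulation).**

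| Handling | Power |
|---|---|
| Healers only, t-test or Mann-Whitney | about 16-17% |
| Unhealed scored at day 84, t-test or Mann-Whitney | about 79-80% |
| Log-rank, unhealed censored at day 84 | about 83% |

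As a check on the last row, 60 + 78 = 138 healing events give 84% by Schoenfeld's formula. A 1,500-run simulation with weekly assessment put the middle row at about 77%, so the loss from day-84 scoring is a few points on any run.

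**5. When follow-up ends early.** Simulation with 125 per arm, no treatment effect, dropout times spread evenly over the 84 days, and the last observed time entered as the healing time.

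| Assumed dropout, control / TOT | Type I error, t-test or Mann-Whitney | Type I error, log-rank |
|---|---|---|
| 20% / 20% | about 0.05 | about 0.05 |
| 30% / 10% | 0.23-0.24 | about 0.05 |

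The inflation needs dropout that differs between arms. The 30% v 10% split is an illustration; the documents give only an overall figure of about 20%.

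**The case against.** The strongest reply is that suitable analyses are already in the plan. Kaplan-Meier, log-rank and Cox are listed for wound healing, time to healing is secondary, and the primary chi-square test of the proportion healed does not use healing times. This stands, and it limits the point to one badly matched test and a missing order of precedence. It does not remove the point, because the sentence naming the t-test or Mann-Whitney for healing time is still there.

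A second reply is that a Mann-Whitney test with all unhealed participants tied at the worst rank is a legitimate comparison of everyone randomised, and that a t-test on day-84 values estimates the restricted mean difference. Both are true if everyone is followed to day 84. The plan does not state such scoring, and it expects about 20% dropout as well as withdrawals from week 4.

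Multiple imputation does not fill the gap as written. It is planned for missing data, whereas a wound observed open at week 12 is censored, and the text does not say that imputation supplies healing times.

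Three stronger readings are tempting and are not supported.

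- *That the plan specifies a healers-only test.* It does not; it is silent, and its intention-to-treat statement points the other way. The 16-17% power belongs to one possible handling.
- *That the tests could only drop the unhealed or pretend that they healed on day 84.* Worst-rank scoring makes no such claim.
- *That the week-4 withdrawal criterion biases the Kaplan-Meier curves by a known amount.* The article does not say that these participants are censored or that their assessments stop, and gives no rate for such withdrawals. Censoring them at stopping would tend to overstate healing, because they leave on account of poor healing, but the size cannot be stated from the documents.

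**Conclusion.** The point holds. A test that takes no account of censoring is assigned to an endpoint that 31% of evaluable participants are expected not to reach by week 12, with no scoring rule and no statement of whether it or the survival analysis governs.

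The consequence depends on the unstated handling: severe if the unhealed are dropped, a few points of power if all are followed and scored at day 84, and a possible type I error problem if follow-up ends early and unequally. The unhealed shares follow directly from the plan's assumed rates. The days and powers rest on assumed constant hazards, and the type I error figures on assumed dropout patterns. The effect is confined to one secondary endpoint. It should be corrected, and it does not threaten the trial's main conclusion.

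**What to change.** In Statistical analysis:

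1. Remove healing time from the t-test/Mann-Whitney sentence and keep that sentence for ulcer area reduction.
2. Name the planned Kaplan-Meier/log-rank and Cox analysis, in all randomised participants, as the analysis of time to healing, with wounds still open at week 12 censored at day 84.
3. If a number of days is wanted, report the restricted mean difference over 84 days.
4. State that participants who stop treatment for poor healing are not censored at stopping. Use their observed healing status from the scheduled 8- and 12-week assessments. Do not fix them as unhealed by rule, since a wound that closes after treatment stops would be misclassified.

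Items 1 and 2 change wording only and use analyses already planned. Item 3 adds one summary. Item 4 needs the scheduled assessments to continue after treatment stops, so the trial team should confirm that they do; it leaves the withdrawal criteria themselves untouched. No change to the sample size or the primary analysis is needed.
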